### Strategies to improve adherence to interventions {11c}

We recruited 4 licensed mental health care professionals (e.g. clinical psychologists, psychiatrists, experienced counsellors) who received a training-of-trainers program with the aim of carrying out supervision for CHANGE facilitators. These trainers/supervisors then delivered a 6-day in-person training, and 1-day online refresher training to the first cohort of facilitators ((*N* = 13, prior to the start of the trial), and a 7-day in-person training to the second cohort of facilitators (*N* = 9). The training program included education on common mental disorders, basic counseling skills, delivery of the CHANGE sessions and self-care. After the training, 16 facilitators were selected for the trial based on their skills, availability and/or geographical location. Two facilitators decided to discontinue their involvement, leaving 14 facilitators for the trial.

During the upcoming trial, the 14 CHANGE facilitators will be divided into two groups, with two supervisors being assigned to each group for online supervision (approximately 2 h per week per group). The supervisors will rotate on a weekly basis within their respective groups to ensure that each supervisor conducts two group supervisions per month, resulting in a weekly group-supervision opportunity for each facilitator. A gradual decrease in frequency of group supervisions is planned throughout the duration of the trial, dependent on the facilitators’ ongoing clinical competencies, decision-making skills, and adherence to protocols.

To carry out fidelity checks, participant sessions for fidelity assessments will be randomly selected by the statistician using Stata 18.0 (College Station, TX, USA) prior to the start of recruitment. An equal number of recordings will be randomly selected across all six sessions, with each participant recorded only once. The M&E lead tracks selected sessions for fidelity recordings on a weekly basis. During consent, participants explicitly give permission for session recordings for quality assurance. Fidelity checklists have been developed based on the strategies and components covered in each of the CHANGE sessions. Fidelity assessments will be completed by the trainers/supervisors.

### Relevant concomitant care permitted or prohibited during the trial {11d}

Concomitant care provided by anyone outside the trial team will be permitted. This may include for participants who are identified as being a perpetrator or victim of intimate partner violence at any time during the trial. These participants will be given additional support via online referral pathways to protection services. Wherever possible, we will document referrals to other forms of care/interventions to allow for sensitivity analysis if needed.

Given the ongoing conflict in Ukraine, all participants will be asked to agree with the safety procedures that are in place before meeting with an outcome assessor, EUC specialist, or facilitator. Including that in the case of an air raid siren taking place in either the CHANGE staff or participants’ location, the online meeting will be stopped, and both participants and the CHANGE staff will prioritise seeking safety. Safety will be sought following local safety directions.

### Provisions for Posttrial care {30}

The 14 facilitators trained to deliver the CHANGE intervention in Ukraine will continue their work and provide care to the community after the trial concludes. Additionally, CETA, which is implemented by the community-based NGO WordsHelp will be available for participants who need additional care. CETA is a treatment program for adults presenting with transdiagnostic problems (e.g. PTSD, depression, anxiety and substance use) developed specifically for use with community workers in low- and middle-income countries and has been proven effective in the context of Ukraine [29]. Participants may be referred to or choose to self-refer to these services. Where participants access CETA during the trial they will be excluded from the analysis.

### Outcomes {12}

The outcome assessors will conduct online data collection using tablets and the electronic data capture system ‘Open Data Kit’ (ODK, https://getodk.org) in a remote format (online, via Zoom, Google Meets, Viber, Telegram, other platforms or via the telephone). Outcome assessment takes approximately 2 h. The outcome assessors, EUC specialists and phone operators each received a separate 3-day online training. During the training, outcome assessors focused on using the outcome measures in ODK, general interviewing skills (including role play exercises), learnt about standard operating procedures, and safety procedures. Two of the outcome assessors were previously involved in the feasibility trial for CHANGE. The EUC specialists and telephone operators each received training in their own SOPs and research ethics. All data collectors receive regular supervision from the field team lead, and none are involved in delivering the intervention.

Outcome assessments will take place during baseline, and 3-months post-randomisation. Similar to the trial in Uganda [23], the primary outcome is the percentage of days abstinent (PDA) at the 3 months’ outcome assessment, adjusted for baseline PDA. Secondary outcomes will include the 3-months assessment in percentage days of heavy drinking, alcohol misuse, psychological distress, depression, anxiety, PTSD, functional disability and perpetration of intimate partner violence. Additionally, quality of life, subjective wellbeing and capabilities-based wellbeing will be measured as secondary outcomes. The outcomes of the trial are summarised in Table 2, with a description of the assessment measures of the outcomes in Table 3. Furthermore, sociodemographic data will be collected during the baseline assessment including level of education, socio-economic status, data on whether they have been displaced and their involvement in military action. At follow-up, we will also collect data on socio-economic status to identify changes. A contamination measure will be used at the 3-month follow up to measure potential contamination of intervention strategies between the two intervention arms. Table 4 describes the socio-demographic data collected at baseline, and Fig. 1 provides an overview of the planned enrolment, allocation, intervention delivery and outcome assessments.

**Table 2 Tab2:** Primary and secondary outcomes of the trial (table adapted from Van Der Boor et al., 2024 [23])

	Source of data (see Table 3 for details of each measure)	
**Primary outcome**	Measure	End point (3 months follow-up)
Percentage of days abstinent	Timeline Followback (TLFB) [31]	X
**Secondary outcomes**		
Percentage days of heavy drinking	TLFB	X
Alcohol Misuse	• Alcohol Use Disorders Identification Test (AUDIT) [26] • Alcohol, Smoking and Substance Involvement Screening Test (ASSIST) [32]	X
Psychological distress	Kessler-10 (K10) [27]	X
Depression	Mental Health Assessment Inventory (MHAI), depression sub-scale [33]	X
Anxiety	Mental Health Assessment Inventory (MHAI), anxiety sub-scale [33]	X
PTSD	Mental Health Assessment Inventory (MHAI), PTSD sub-scale [33]	X
Functional disability	Mental Health Assessment Inventory (MHAI) [33]	X
Perpetration of intimate partner violence	United Nations Multi-Country Study on Men and Violence [34]	X
Health economics indicators	• EuroQol 5 dimensions 5 Levels (EQ-5D-5L) [42] • Subjective wellbeing [35] • Oxford Capabilities Mental Health questionnaire (OxCAP-MH) [36] • User cost questionnaire	X

**Table 3 Tab3:** Details on CHANGE Intervention Trial Outcome Measures (table adapted from Van Der Boor et al., 2024 [23])

Instrument	Description	Outcome	Contextual validity
Timeline Followback	Diary method to retrospectively assess daily estimates of drinking	Percentage days abstinent (PDA): Proportion of past 14 days on which participant was abstinent; analysis based on distribution. It also allows measurement of percentage of days of heavy drinking	Validated for alcohol use assessment including in Ukraine [43]
AUDIT	Ten-item questionnaire to measure alcohol intake, identify potential dependence on alcohol; and experiences of alcohol-related harm. Each item assessed on a scale of 0 to 4	Mean score, and dichotomous (medium vs. high risk) as secondary outcome	Validated for the current project with Ukrainian and Russian speaking men living in Ukraine, paper forthcoming
ASSIST	Eight-item screening questionnaire on estimates of alcohol use, tobacco products, and other drugs across the lifetime and in the past three months. Measured on a scale of 0 to 7	Mean score	Validated in a multisite international study covering Australia, Brazil, India, Thailand, United Kingdom, USA, and Zimbabwe [44]
K10	Ten-item scale on non-specific psychological distress, scored on a scale of 1 to 5	Mean score	Validated in Ukraine including amongst war-affected Ukrainians [45, 46]
MHAI	Thirty-two item scale on depression, post-traumatic stress, anxiety, functioning and alcohol use	Mean score	Locally validated measure with good psychometric properties [33]
United Nations Multi Country Study on Men and Violence	Eleven items are used to measure the prevalence of perpetration of violence in the last 3 months. The items are assessed on a scale of 1 to 4, or 1 to 7	Prevalence of IPV split by type of intimate partner violence (physical, sexual)	Previously validated in Bangladesh, China, Cambodia, Indonesia, Sri Lanka, and Papua New Guinea [34]
EQ-5D-L	Five item questionnaire for measuring health related quality of life across five dimensions: mobility, self-care, usual activities, pain/discomfort, and anxiety/depression, rated on the day. A five-level response option is used	Locally adjusted scoring algorithm	Validated across different contexts including Ukraine (https://euroqol.org/register/obtain-eq-5d/available-versions/)
Subjective Wellbeing	Five items on subjective wellbeing, measuring overall life satisfaction, whether the things the respondent does are worthwhile, and affect; scored on a scale of 1 to 5	Locally adjusted scoring algorithm	Used across countries in the Gallup world poll which covers more than 150 countries, including Ukraine (https://www.gallup.com/analytics/349487/world-happiness-report.aspx)
OxCAP-MH	Sixteen item index on wellbeing, covering various domains of individual well-being including overall health, enjoying social and recreational activities, friendship, and support, having suitable accommodation etc. Scored on a scale of 1 to 5	Mean score	Has been contextually translated and validated by the current research team in Ukraine into Ukrainian and Russian spoken in Ukraine (publication forthcoming)
User Cost Questionnaire	Fifteen item measure on household expenditure specifically designed for this trial to measure the opportunity cost of participating in the CHANGE intervention	The opportunity cost of participating in the CHANGE intervention	Specifically designed and piloted for this trial. Based on the iMTA productivity loss of cost questionnaire

**Table 4 Tab4:** Sociodemographic data collection

Construct	Measure
Education	Education (no school, primary, secondary, tertiary education, etc.)
Age	In years
Socio-economic status	Self-perceived relative socio-economic status (e.g., income level as multiple-choice question)
Trauma exposure	Life Events Checklist
Use of local substances (e.g., khat, tobacco, marijuana, opioids, synthetic drugs etc.)	Measured developed for study or standardized measure (e.g., ASSIST)
Displacement status	Multiple-choice answer
Length of time displaced	Open-ended answer
Frequency of movement	Open-ended answer
Veteran status	Open-ended answer
Length of military duty	Open-ended answer
Frequency of military duties	Open-ended answer
Marital status	Multiple-choice answer
Having kids	Multiple choice answer
Number of Kids	Multiple choice answer
Separation from wife/kids due to displacement	Multiple-choice answer
Geographical location	Multiple-choice answer
Occupation/work status	Multiple-choice answer
Use of psychotropic medications (e.g., antipsychotics, antidepressants)	Multiple-choice answer

**Fig. 1 Fig1:**
[figure not shown]
SPIRIT figure including planned enrolment, allocation, intervention delivery and outcome assessments for the CHANGE intervention (adapted from Van Der Boor et al., 2024 [23])

The Enhancing Assessment of Common Therapeutic factors (ENACT) tool [30] will be used to measure the competency of the facilitators to deliver CHANGE through the Ensuring Quality in Psychological Support (EQUIP) platform. These competency assessments were carried out before the start of the trial with 2 cohorts of facilitators by 3 trainers/supervisors who completed their training in rating and using the EQUIP system. The first assessment with the first cohort of facilitators was conducted 2 months after training completion. Facilitators were asked to perform the intervention in pairs and have them recorded independently (via ZOOM) and uploaded to SharePoint. Similarly, we used the same approach with the second assessment for the first cohort, completed before the RCT began. With the second cohort of facilitators, extra time was allocated during the training for the competency assessment activity in person while all three raters were present to conduct the assessment.

We will conduct a mixed-methods process evaluation during the trial, including data collection on competency of facilitators, fidelity and feasibility of delivery, appropriateness, dose, recruitment, retention/completion and acceptability. A nested qualitative study will be carried out with semi-structured interviews taking place at 3-months post-randomisation to further understand the implementation process. Interviews will be done with supervisors (*N* = 4), facilitators (*N* = 14), outcome assessors (*N* = 2), phone operators (*N* = 2), participants in the control arm (*N* = 20), participants in the intervention arm (*N* = 20), family members of participants (*N* = 20) and as many participants as possible who dropped out from the intervention group. Topic guides will be used to explore the processes which will include themes on engagement with CHANGE, recruitment and attendance, program delivery, perceived effectiveness and helpfulness, acceptability of CHANGE for participants and facilitators, feasibility of delivery, as well as opportunity costs in attending CHANGE.

### Participant timeline {13}

Community-based recruitment will be carried out with the help of the implementing partner and NGO WordsHelp who will recruit within their networks and member base using digital flyers and dissemination of information on Facebook and Instagram pages. Furthermore, recruitment will be facilitated online using social media platforms including Facebook, Telegram, Instagram and others by making available a flyer (the advertisement of the trial with the contact details (online registration form or phone number), and through mass media activities. When participants get in touch with the research team, interested participants will be contacted via the telephone by the research assistants responsible for the initial contacting (phone operators). The phone operators will establish whether the participant has a good understanding of the study, collect additional information to see if the person can benefit from participation, check the technological means to participate (e.g. having a stable internet connection, owning a laptop tablet or phone), their platform of preference (e.g. Google Meets, Zoom, telephone) and a date and time to meet with the data collector for eligibility screening. After the initial contacting, the phone operators will send a digital copy of an information sheet and the text of consent form to participants via messaging app or email to read before the remote meeting with data collector.

Outcome assessors will meet the participant at the date, time and on the platform of preference previously established. Participants are given a short safety briefing, including an overview of potential safety risks, and instructions on what to do in high-risk situations (e.g. missile attacks or air raids during the session), and are given the opportunity to ask questions. Participants are asked to give verbal informed consent before the eligibility screening is conducted. Written consent is not requested given the security concerns of signing documents. If verbal consent is provided, the outcome assessors go through the screening tool, and sociodemographic questions with the participant taking note of their responses using ODK. If eligibility criteria are met, outcome assessors continue to the baseline assessment.

Following the baseline assessment, an EUC specialist will join the call or set up a separate call with participant (on a separate day) to go through an electronic information pamphlet (detailing information on reducing alcohol intake and managing psychological distress as well as outlining ways of contacting alternative psychological services). The EUC specialist will also carry out the randomisation procedure, as detailed in the section below. Those randomised to the intervention arm will receive their first CHANGE session the week after (see Fig. 1).

Participants will be followed up at 3-months after baseline for the outcome assessment. Additional qualitative interviews will be carried out at 3 months follow-up using a purposive sampling strategy. Qualitative interviews will be carried out with all intervention facilitators ( *N* = 14), supervisors (*N* = 4), outcome assessors (*N* = 2) and phone operators (*N* = 2), in addition to family members of participants (*N* = 20), participants in the intervention arm (*N* = 20), participants in the control arm (*N* = 20) and as many participants who dropped out as possible (Fig. 2).

**Fig. 2 Fig2:**
[figure not shown]
Consolidated standards of reporting trials (CONSORT) diagram (adapted from Van Der Boor et al., 2024 [23])

### Sample size {14}

A sample size of 500 enrolled participants (250 in each arm with 1:1 allocation) will provide 90% power (alpha = 0.05) to detect a difference in participants’ PDA from alcohol at follow-up of 55% in the EUC arm vs 68% in the CHANGE arm. This assumes participants’ PDA from alcohol is distributed with a standard deviation of 37% in both arms [37]. Both the effect size and the standard deviation are based on the Counselling for Alcohol Problems (CAP) trial (54% vs. 69%). The sample size calculation accounts for 20% loss to follow-up at 3 months and is based on Nadkarni et al. 2017 [37].

### Recruitment {15}

We focused on Ukraine government-controlled territories to mitigate against potential physical and psychological risks for participants residing in territories currently controlled by the Russian military and Crimea. By government-controlled areas, we refer to areas currently under the administrative and military control of the Ukrainian government. Temporarily occupied territories including parts of Donetsk and Luhansk oblasts, Crimea and parts of Zaporizhzhia, Mykolaiv, Kharkiv and Kherson oblasts were excluded. If the status of these or other territories changes during the trial, their inclusion or exclusion will be adjusted according to this definition. Four different recruitment strategies will be used across government-controlled territories in Ukraine. Firstly, we will disseminate information about the trial on various social media platforms, channels and groups (Telegram, Facebook, Instagram) and mass media: broadcast on the radio, posting news about the trial, interviews and other activities, in addition to setting up partnerships with community-based NGOs, veteran unions and government organizations (e.g. social services) to set up referral pathways to CHANGE. Secondly, community recruiters based at WordsHelp and other local community organisations will use their local connections to divulge information on the CHANGE trial for recruitment purposes. Thirdly, healthcare providers trained in the use of the Mental Health Gap Action Programme (mhGAP) and neurologists will be approached to refer patients who present symptoms of alcohol misuse and other comorbidities to the CHANGE trial. Lastly, digital recruitment flyers will be used for dissemination for partner organizations and social media usage (e.g. Facebook, Instagram), which will include an online registration form to the trial study. Snowball sampling will be used throughout the recruitment process to recruit additional participants. Participants will be offered 250 UAH worth of phone credit or local grocery store card per assessment (screening and follow up). They will also receive the same amount for each session attended (for those randomised into the intervention arm), provided at the end of the treatment course. The date of the first recruitment was 4 September 2024.

## Assignment of interventions: allocations

### Sequence generation{16a}

Stata 16.0 statistical software (College Station, TX, USA) will be used to generate a randomisation sequence by an independent statistician who is not part of the trial team. Randomisation will be blocked of 4, 6 or 8 participants in a random order. Participants will be individually randomised 1:1 to both arms of the trial by the EUC specialist following baseline assessment [23].

### Concealment mechanism {16b}

Concealment of allocation will be ensured using sequentially numbered virtual envelopes. Microsoft Lists will be used to store the randomisation sequence, which will only be accessible to the team members that are unmasked throughout the trial. Virtual envelopes will be assigned to the participant in the order that participants are enrolled into the study. The virtual envelope will display the envelope ID and status (locked/unlocked). The EUC specialist will unlock the respective virtual envelope, after which the envelope status automatically updates to unlocked, the date and time of unlocking is recorded and the randomisation code and allocation is displayed. All actions related to unlocking the virtual envelopes will be tracked using version control mechanisms. This mechanism improves procedural accuracy by demonstrating compliance to standard operating procedures, ensuring there are no errors in the randomisation process. All EUC specialists will be trained on the importance of maintaining the randomisation sequence and weekly data monitoring checks will be done to identify irregularities in the allocation sequence in which envelopes are opened.

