### Implementation {16c}

The randomisation database on Microsoft Lists will be prepared by the data manager who is unmasked throughout the trial. The EUC specialists will access the virtual envelopes to enrol participants online, as described above. Once the virtual envelope is unlocked, the EUC specialist will read the text displayed inside the envelope and describe the next steps depending on the allocation of the participant. The EUC specialists will also deliver the EUC online to all of those who are enrolled. Given that all procedures will be conducted remotely, we do not expect any accidental unmasking to take place for the outcome assessors, principal investigators (PIs) or others who are masked.

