## Assignment of interventions: masking

### Who will be masked? {17a}

The PI (DF), site PI (SB), co-investigators and outcome assessors will be masked to treatment allocation during the trial. The trial statistician will be masked until the primary analysis is complete. Participants, facilitators, EUC specialists, qualitative researchers and the research director will be unmasked. The field team lead and data manager will also be unmasked as the data manager is responsible for developing the virtual envelopes through Microsoft Lists and the field team lead is responsible for the overall research assistant team support and supervision, carrying out routine data checks and monitoring.

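### As written, the access rule for the stored randomisation sequence includes the EUC specialists who randomise every participant, and so conflicts with the locked-envelope concealment described in the same section

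*Protocol article*

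**What the plan says.** All references are to the protocol article.

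- **Concealment mechanism {16b}** states that concealment is ensured through sequentially numbered virtual envelopes, and sets the access rule: "Microsoft Lists will be used to store the randomisation sequence, which will only be accessible to the team members that are unmasked", the sentence ending with the qualifier that this means throughout the trial.
- The same section describes what a locked envelope shows: "The virtual envelope will display the envelope ID and status (locked/unlocked"). The allocation appears once the EUC specialist unlocks the envelope, and the date and time are recorded. Unlocking is tracked by version control, and the order of opening is checked weekly.
- **Who will be masked? {17a}**: "Participants, facilitators, EUC specialists, qualitative researchers and the research director will be unmasked". The next sentence adds the field team lead and the data manager.
- **Sequence generation {16a}**: "Participants will be individually randomised 1:1 to both arms of the trial by the EUC specialist following baseline assessment". Blocks are of 4, 6 or 8 in random order, and an independent statistician generates the sequence.
- **Implementation {16c}**: "The EUC specialists will access the virtual envelopes to enrol participants online, as described above". The data manager prepares the list.
- **Participant timeline {13}**: after the baseline assessment, "an EUC specialist will join the call or set up a separate call with participant", the latter on another day.
- **Explanation for the choice of comparators {6b}**: there are two EUC specialists.

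**The concern.** Masking and concealment answer different questions. Masking status decides who may know an allocation after it has been made. Concealment requires that whoever enrols and assigns cannot know it beforehand. The access rule uses the first criterion to settle the second, and so takes in the staff who perform the randomisation.

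Foreknowledge matters here for two reasons. Someone who knows the next allocation can influence which eligible participant receives it, and analysis cannot reliably repair selection introduced at that point. In addition, participants are unmasked and the primary outcome, percentage of days abstinent, is self-reported. A difference between arms in who was enrolled would be hard to separate from a treatment effect.

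**Working it through.** The plan gives no figure to reproduce on this point, so the check compares sections.

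**1. Who falls inside the access rule.** {16b} names team members unmasked throughout the trial. {17a} gives the unmasked staff as facilitators, EUC specialists, qualitative researchers, the research director, the field team lead and the data manager.

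**2. Who randomises.** {16a}, {16b} and {16c} all give this task to the EUC specialists. They therefore appear both among those with access and among those who assign.

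**3. Whether another section narrows the rule.** The article uses similar wording in three other places:

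- {16c} applies it to the data manager alone.
- Data management {19} applies it as a group label for those who may open the SharePoint site linking names to IDs.
- The retention section {18b} limits the separate enrolment database to particular members among the unmasked.

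The authors thus express a subset where they intend one. {16b} uses the plural and sets no such limit, and no section bars EUC specialists from unopened rows.

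**4. Whether the stated safeguards fill the gap.**

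- The locked display conceals only if the list behind it cannot be read. That is what the access rule leaves open.
- Version control is described for actions related to unlocking. Reading a row is not an unlocking action.
- The weekly check concerns the order in which envelopes are opened. Envelopes opened in perfect order are compatible with someone having read ahead.

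**5. Whether there is room to act on foreknowledge.** Masked outcome assessors complete consent, screening and baseline first, so eligibility is settled before the EUC specialist acts. What remains is the order of people already found eligible. Envelopes follow the order of enrolment, the EUC specialists enrol, and their call may be placed on a separate day. The room is limited but not nil.

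**6. What a readable list would add.** With the list readable, all 500 upcoming allocations are known (100%). The comparison is a person who sees only past allocations, guesses the arm so far under-represented, and tosses a coin when the arms are level. For a block of size 2m, the expected number of correct guesses is m + ½(4^m / C(2m, m) − 1):

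- block of 4: 2 + ½(16/6 − 1) = 2.833
- block of 6: 3 + ½(64/20 − 1) = 4.100
- block of 8: 4 + ½(256/70 − 1) = 5.329

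With the three sizes equally likely (an assumption; the article says only random order), the share correct is (2.833 + 4.100 + 5.329) / (4 + 6 + 8) = 12.262 / 18 = 0.681. A simulation of 4,000 sequences of 500 gave 0.319 for the opposite guess, that is 1 − 0.319 = 0.681 for this one.

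Over 500 allocations this is about 341 correct guesses, against 250 by chance and 500 with the list open. These figures describe predictability. They do not estimate bias.

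**The case against.** The strongest reply is that {16b} describes a working mechanism: an envelope that shows only its number and status until it is opened, with each opening time-stamped and tracked. A rule that only certain people have access sets a ceiling and need not give each of them full read rights. EUC specialists need some access to the list simply to unlock envelopes, and the wording may mean no more than that. {16c} uses the same qualifier for the data manager, who builds the list. Row-level permissions are also the kind of detail that an article leaves to standard operating procedures.

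Much of this stands, and it rules out several stronger readings that a reader might infer:

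- **That allocation is in fact not concealed from those assigning it.** No section says that EUC specialists can read locked rows, and the envelope description points the other way.
- **That re-ordering of participants could never be detected.** Unlock times are recorded, baseline data are uploaded at the end of each working day, and {19} includes a weekly review of randomisation order. The material for comparing baseline order with unlock order exists, although the article does not describe that comparison.
- **That EUC is delivered with knowledge of the arm.** {13} describes the pamphlet before the randomisation, and {16c} fixes no order. Arm-aware delivery is possible but not shown, and it would be a matter of performance bias.
- **That allocations leak to the assessors through the field team lead.** {12} says that "All data collectors receive regular supervision from the field team lead", but no section describes such leakage.

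What the reply does not remove is the conflict itself. The missing detail could be left to a procedure if the article were silent. It is not silent: it states an access criterion, and that criterion includes the people who randomise.

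**Conclusion.** The point holds as a conflict in the protocol text. The access rule in {16b}, read with {17a}, opens the stored sequence to the EUC specialists who randomise every participant, and to facilitators, the research director and the field team lead, for whom the article states no need to see unopened allocations. This is incompatible with the locked-envelope mechanism and with the claim that concealment is ensured. The described checks would not detect someone reading ahead.

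It does not follow that concealment has failed. The permissions in use are not reported, and eligibility and baseline are settled by masked assessors beforehand, which narrows any effect to the order of already eligible men. If the rule was implemented literally, all 500 allocations, handled by two specialists, were open to foreknowledge. If unopened rows were already restricted, only the wording needs correcting. No size of bias can be given from the document. The conclusion assumes that the plural wording in {16b} means the unmasked staff listed in {17a}, which is its plain reading.

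**What to change.** Replace the access criterion in {16b} with one based on role:

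- Unopened allocations are readable only by staff with no part in enrolling or randomising, namely the independent statistician and the data manager who builds the list.
- EUC specialists see the envelope number and status, and one allocation at a time after an irrevocable, time-stamped unlock.
- Other unmasked staff see only rows already unlocked.

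Confirm and document the permissions in force since the first recruitment on 4 September 2024. If anyone who randomises could read unopened rows, report this and compare the order of baseline assessments with the order of unlocking.

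As a secondary step, state that the EUC session is completed before the envelope is unlocked and that the outcome assessor has left the call by then. {13} and {16c} leave this order open.

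The cost is a change of list permissions, a few sentences in the protocol and operating procedure, and a one-off review of past permissions. No extra staff are needed. If the change is treated as a protocol amendment, it needs the two ethics approvals named in {25}. Recruitment was expected to finish in 2026, so a correction may still protect later allocations.
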